### Sample size calculation

Study sample size is evaluated with respect to the primary outcome (difference in the challenge Y-BOCS between tDCS and Sham), given that the aim is to estimate the likely effect size of a future trial. We assume that the sample will be representative of the population, and that the observed variance, and Y-BOCS scores in each condition will allow for estimation of a typical group comparison. Given that there are only 4 exposures of tDCS in each study condition, with 4 weeks between exposures, we assume no carry-over effects, which will be tested using a mixed model. Each tDCS target (OFC and SMA) will be considered independently against Sham. Published estimates of effect size vary widely [45]; thus, a conservative estimate of *d* = .3 is assumed. Following Cocks and Torgersen [51], assuming *α* = 0.05, 1 – *β* = 0.80, a sample size of 20 per group allows detection of a lower limit of *d*’ > 0.1 for an expected effect size *d*’ = 0.3. An additional 5 patients will allow for a 25% dropout.

It is estimated that approximately 25 patients will be recruited from a pool of 200 patients identified from screening, giving power to estimate the ascertainment ratio to within ± 6%. The proportion of missed treatment sessions is expected to be less than 20% from a total of 206 sessions, giving a precision within ± 6%. At the outset of the study, it is not possible to estimate the likely number of reported adverse events (safety), which is expected to be low, and cannot therefore estimate the likely precision of estimation.

Time-dependent changes in the Y-BOCS scores, and in the CANTAB test scores will be considered using standard paired comparisons (*t* test). A sample size of *N* = 20 allows for detection of an effect size *d*’ = .65 with power 1 – *β* = .78, and an effect size *d*’ = .77 with power 1 – *β* = .90. A time-dependent model will be evaluated (mixed model) to examine trends over time, but with limited power.

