##### Likely effect size

The primary focus on comparisons will be on the potential effect size at 24 h after the final stimulation in each treatment condition. The observed and the lower limit for the effect size for the OFC and SMA targets will be evaluated with respect to the Sham condition, assuming that no carryover effects are observed in the crossover design (mixed model). A lower limit for effect size of < 0.1 will indicate a positive signal to proceed. Where possible, treatment target differences will be adjusted in a mixed model to account for baseline values of key patient variables.

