### Progression to a full trial

The decision whether to progress will be based on consideration of all findings, but principally on the following data:The acceptability of tDCS will be considered throughout the ascertainment ratio (target 10%), willingness of clinicians to recruit to the study, and the numbers of patients citing tDCS as the reason for refusal (< 20%).Feasibility of recruiting sufficient patients in a multicentre national study will be evaluated in relation to the population size in each of the study centres, and extrapolation to the number of centres required to achieve the required sample size for a full-scale trial.The study targets a lower limit for the effect size of tDCS > .1, giving confidence that the effect of tDCS is at least .3. The study will enable evaluation of the superiority of the two tDCS target sites (OFC or SMA, given limited power).Differences between the targets will be considered in the light of differences in the profile of the neurocognitive tests indicating that the changes are consistent with the hypothesised effects (SMA target: motor impulsivity; OFC target: cognitive flexibility, cooperation).

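### The efficacy go signal has its inequality reversed: the analysis section says to proceed if the lower limit is below 0.1, the progression section if it is above 0.1

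*Protocol article*

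**What the plan says.** Three sections of the protocol article state a threshold for the lower limit of the effect size against sham.

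- **Likely effect size** (analysis of secondary outcome). For each target against sham, with the main focus at 24 h after the final stimulation: "A lower limit for effect size of < 0.1 will indicate a positive signal to proceed".
- **Progression to a full trial**: "The study targets a lower limit for the effect size of tDCS > .1", followed by the interpretation "giving confidence that the effect of tDCS is at least .3".
- **Sample size calculation**: "a conservative estimate of *d* = .3 is assumed", and the study is sized to give "a lower limit of *d*’ > 0.1 for an expected effect size *d*’ = 0.3".

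The sample size section and the progression section agree with each other. The analysis section states the opposite. None of the three gives the confidence level or sidedness of the limit; the sample size section gives only α = 0.05 and 80% power.

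**The concern.** Except for a limit of exactly 0.1, every result that passes one rule fails the other. The effect sizes are given as positive values and a higher limit is treated as favourable, so no sign convention rescues the analysis section. If improvement were coded as negative, the rule would need an upper limit below -0.1, which is not what is written.

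This limit is the only numerical efficacy threshold among the progression criteria. A go rule that exists in both directions allows either decision to be defended once the data are known, and read literally the analysis section favours targets that do nothing.

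The interpretation in the progression section is a second, smaller error. A lower confidence limit above 0.1 supports an effect above 0.1. To support an effect of at least 0.3, the limit itself would have to reach 0.3.

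**Working it through.** **Inputs from the protocol.** Evaluable n = 20 (25 less the dropout allowance), each patient receiving both conditions compared; expected d = 0.3; threshold 0.1; each target compared with sham separately.

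**Assumptions, because the protocol is silent.** d is in units of the SD of the paired difference, so SE = 1/√20 = 0.224. The main case is a one-sided 80% limit (z = 0.842), with a two-sided 95% limit (z = 1.960) to show the range. Normal approximation.

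**Step 1: reproduce the planned figure.** Lower limit = d − z × SE.

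- One-sided 80%: 0.3 − 0.842 × 0.224 = 0.112, which is above 0.1.
- The n at which the limit is exactly 0.1: (0.842/0.2)² = 17.7, so 18, close to the stated 20.
- Two-sided 80%: 0.013. One-sided 95%: −0.068. Two-sided 95%: −0.138.
- Two independent groups of 20, one-sided 80%: 0.034.

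Of these, only the paired, one-sided 80% reading reproduces the plan's statement, and it does so in the above-0.1 direction. An observed effect equal to the one planned for would therefore fail the rule in the analysis section.

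If d is instead scaled by the between-patient SD, the one-sided 80% limit at d = 0.3 runs from 0.077 (within-patient correlation 0.3) to 0.181 (correlation 0.8). At correlation 0.5 the two scales coincide.

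**Step 2: chance of a go under each rule.** The limit exceeds 0.1 when the observed d exceeds 0.1 + z × SE. That cut-off is 0.288 for the one-sided 80% limit and 0.538 for the two-sided 95% limit. For true effect d,

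P(limit < 0.1) = Φ[(0.1 + z × SE − d)/SE].

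| True d | As written, one-sided 80% | Reversed sign, one-sided 80% | As written, two-sided 95% | Reversed sign, two-sided 95% |
|---|---|---|---|---|
| −0.3 | 99.6% | 0.4% | about 100% | about 0% |
| 0 | 90% | 10% | 99% | 0.8% |
| 0.1 | 80% | 20% | 97.5% | 2.5% |
| 0.3 | 48% | 52% | 86% | 14% |
| 0.65 | 5% | 95% | 31% | 69% |
| 1.0 | 0.1% | 99.9% | 2% | 98% |

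With the noncentral t distribution on 19 degrees of freedom, the as-written column for the one-sided 80% limit gives 90%, 48% and 6% at d = 0, 0.3 and 0.65, essentially the same. In every version the chance of a go under the written rule falls as the true benefit rises.

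**Step 3: the claim about 0.3.** With the one-sided 80% limit, a limit just above 0.1 corresponds to an observed d of about 0.29. So 0.3 is roughly the point estimate at the threshold, not a bound on the true effect. A limit of 0.3 would need an observed d of 0.3 + 0.842 × 0.224 = 0.488.

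**The case against.** The strongest reply is that this is a one-character slip. The correct direction appears twice, once in the section that governs progression, and that section weighs all findings rather than applying an automatic gate. A reader with the whole document could infer the intent. That lowers the practical risk, but the wrong sign stands where the analysis of this estimate is defined, and nothing says which section takes precedence.

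Four narrower points stand:

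- At the planned effect of 0.3, the two directions are close to a coin flip with a one-sided 80% limit (48% against 52%). The reversal is stark only for null, harmful or clearly larger effects.
- The percentages depend on a confidence level that the protocol does not give, which is why a range is shown.
- Choice between the two targets does not rest on this limit. The protocol also compares them directly by paired tests and considers the neurocognitive profile.
- The 0.3 in the progression section may be loose shorthand for the expected or observed effect. The protocol says the observed magnitude and SD will inform the next sample size; it does not say that 0.3 will be carried forward as established. Harm to the definitive trial from this phrase is therefore possible, not shown.

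**Conclusion.** The concern holds. The go signal in the analysis section is reversed relative to the sample size and progression sections, and only the above-0.1 direction is consistent with the planned 20 evaluable patients. As written, a target with no effect is given a go about 90% of the time (99% with a two-sided 95% limit), while one with d = 0.65 is given a go about 5% of the time (31%). These figures assume n = 20 paired, effects in SDs of the paired difference and a normal approximation. The direction of the error depends on none of this. It must be corrected before the analysis, because it is a decision threshold. The statement that a limit above 0.1 supports an effect of at least 0.3 is also wrong as inference, but is a lesser matter of wording.

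**What to change.** 1. In the section on likely effect size, reverse the inequality so that a lower limit above 0.1 is the positive signal, in line with the other two sections.
2. In the same sentence, state the confidence level and sidedness of the limit and the SD used to standardise the effect. If the intended limit is one-sided 80%, as the planned size suggests, say so.
3. In the progression section, replace the claim about an effect of at least 0.3 by the statement that the limit gives confidence, at the stated level, that the effect exceeds 0.1.

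The cost is two wording corrections plus the definition of the limit. The design, sample size and data collection do not change. If the full protocol or analysis plan carries the same sentence, correct it there too.

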##### Duration of effect

Change over time will be evaluated separately for the OFC and SMA targets using paired tests, identifying the time point (1, 2 and 4 h or 1, 7 and 14 days) at which the Y-BOCS returns to pre-stimulation levels. A mixed model may be evaluated where this may provide additional useful information about the trajectory of the Y-BOCS score over time (growth models).

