### Stimulation schedules

The stimulation protocol in FEATSOCS has been designed according to expert recommendations regarding the safety of tDCS, developed for research ethics committees and Institutional Review Boards, as well as in clinical practice [43]. The application of tDCS has presented minimal risk in numerous research or clinical studies when applied within standard parameters. Minimal risk means there have been no serious adverse events, that common adverse effects such as reddening of the skin are mild and short-lived, and that reasonable efforts at assessment have determined there is no evidence of brain damage. Standard parameters to date mean that (1) the current is less than 2.5 mA, (2) it is applied through electrodes that are known to minimize skin burns at the specific current level, (3) the current application duration is less than 20–60 min per session, and (4) sessions are not more frequent than twice per day [42, 43]. In line with these recommendations, each participant will receive two 20-min stimulations separated by 4 h on Day 1 and on Day 2 of each session comprising:Cathodal tDCS 2 mA to the bilateral SMACathodal tDCS 2 mA to the left OFCSham tDCS to the OFC or SMA

The courses will be allocated in a randomised and counterbalanced order. Each 2-day course of tDCS will be spaced 4 weeks apart to avoid carry-over effects, and allow for the duration of effect to be evaluated. Patients will be assessed before each stimulation, up to 4 h afterward, with the assessments at 4 h after the second stimulation may be conducted over the phone, and then at 24 h and 7,14 and 28 days following tDCS stimulation.

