##### Evaluation of neurocognitive test

The effects of the tDCS target on neurocognitive function will be evaluated for each target and test separately, by documenting test scores at each time point (baseline, 3 h). Differences in the profile of effect will be evaluated on the test dimensions dependent on the target (SMA target: motor impulsivity; OFC target: cognitive flexibility, cooperation). Comparison will proceed using paired tests, and if study power permits, mixed models.

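### Duration of effect is judged within each active target against its own pre-stimulation score, with no stated sham contrast beyond 24 h and no rule for reading a return

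*Protocol article*

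**What the plan says.** Under Duration of effect, the protocol article states: "Change over time will be evaluated separately for the OFC and SMA targets using paired tests, identifying the time point". Six candidate times are listed, three on the day of stimulation and three over the following two weeks: "1, 2 and 4 h or 1, 7 and 14 days". The time being sought is described as the one "at which the Y-BOCS returns to pre-stimulation levels". Sham is not named. The section then offers a growth model as an option: "A mixed model may be evaluated where this may provide additional useful information about the trajectory".

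The Sample size calculation section names the test: "Time-dependent changes in the Y-BOCS scores, and in the CANTAB test scores will be considered using standard paired comparisons", by t test. It also says that a time-dependent mixed model will be evaluated with limited power, and gives no model terms.

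Under Evaluation of neurocognitive test, effects "will be evaluated for each target and test separately, by documenting test scores at each time point (baseline, 3 h"), and then "Comparison will proceed using paired tests, and if study power permits, mixed models". Differences in profile between the two targets are also to be examined.

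Sham appears in two related places. Effect of tDCS estimates scores in all three conditions at all time points, but the only paired comparison it names is OFC against SMA. Likely effect size contrasts each target with sham at 24 h after the final stimulation.

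Table 1 gives one assessment schedule for all three courses, sham included. Stimulation schedules lists follow-up at 24 h and "7,14 and 28 days following tDCS stimulation".

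**The concern.** A paired test of a post-stimulation score against the same course's baseline measures total change. That total contains any specific effect of current, any placebo response and any drift over time. Sham is in the design to separate these, yet the duration analysis as written does not subtract it.

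The tool is also poorly matched to the question. A paired test can show that change is present, but a non-significant result does not show that it has gone. With no margin and no interval rule, the reader is left to take the time at which significance is lost as the time of return.

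The two problems push in opposite directions. Unsubtracted sham change lengthens the apparent duration, and low power shortens it. The Secondary objectives say the duration result is to be used to space treatments. The neurocognitive profile, which has the same gap, is listed under Progression to a full trial.

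**Working it through.** **Inputs from the protocol article (Sample size calculation).** n = 20 evaluable; α = 0.05, taken as two-sided because the article does not say; expected effect d = 0.3; stated paired-test power 0.78 at 0.65 and 0.90 at 0.77.

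**Assumed inputs.** A standardised change of 0.5 or 0.8; correlation between change scores at different times of 0.3 to 0.8. The article's 0.3 is an effect against sham. It is used here only as a benchmark for the size of within-course change.

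**1. Reproduce the plan's figures.** Paired t test, 19 degrees of freedom, critical value 2.093, noncentrality d × √20.
- d = 0.65: power 0.787 (stated 0.78).
- d = 0.77: power 0.904 (stated 0.90).

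The stated figures are correct. A one-sided test would give 0.876 and 0.953, so two-sided is the right reading.

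**2. A persisting effect missed at a single time point.**
- d = 0.3: power 0.247, missed 1 − 0.247 = 0.753, about 75%.
- d = 0.5: power 0.565, missed 1 − 0.565 = 0.435, about 44% (0.4355 before rounding).

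**3. A persisting effect over days 1, 7 and 14.** Simulation with n = 20, three equally correlated change scores and a constant true change of 0.5 that never wanes. The share of trials with at least one non-significant point by day 14:

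| Correlation (assumed) | Share |
|---|---|
| 0.3 | 0.747 |
| 0.7 | 0.635 |
| 0.8 | 0.593 |

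So about 59% to 75% of such trials would show an apparent return, although nothing has waned.

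**4. The other direction: no specific effect, but a change shared with sham.** The within-target test is significant with the same power function:

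| Shared change (assumed) | Within-target test significant | Active-minus-sham test significant |
|---|---|---|
| 0.3 | 25% | 5% |
| 0.5 | 57% | 5% |
| 0.8 | 92% | 5% |

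The last column stays at 5% because the shared change cancels in the difference.

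**5. What a sham contrast does not cure.** The 95% half-width at n = 20 is 2.093/√20 = 0.47 SD of the paired difference.

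**6. Why a cut-off of 0.1 on the point estimate would not help.** The standard error is 1/√20 = 0.22 SD.
- A true 0.3 reads below 0.1 with probability Φ((0.1 − 0.3)/0.224) = Φ(−0.89), about 19%.
- A true zero reads above 0.1 with probability 1 − Φ(0.1/0.224) = 1 − Φ(0.45), about 33%.

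In the article 0.1 is a lower limit for the effect size, not a margin for a point estimate.

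**The case against.** The strongest reply is that the protocol already holds most of what is needed. The sham trajectory is estimated at all time points, each target is contrasted with sham at 24 h, and a time-dependent mixed model is planned. Duration is a secondary outcome in a feasibility study that admits limited power, and it is not among the principal progression criteria. All of this is true and lowers the weight of the point. It does not supply a stated sham contrast at the other time points, and neither description of the mixed model mentions sham.

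Several stronger readings are tempting but not supported:
- *The sham data are unused.* They are estimated at every time point; what is missing is a formal contrast other than at 24 h.
- *The plan equates non-significance with return.* It does not say so. That is an inference from the only tool named, and an analysis plan not shown here might define the rule.
- *Paired tests lose patients who lack another course.* A within-course pair needs one course only, and a constant period shift cancels in it. That loss would apply to the OFC against SMA comparison.
- *All neurocognitive practice counts as tDCS effect.* The planned between-target comparison cancels practice common to both courses. It cannot show that either target differs from sham.
- *Regression to the mean from the Y-BOCS entry score of 20 inflates every course.* Y-BOCS is retaken at each course's baseline, so entry selection bears mainly on the first course, and order is counterbalanced.
- *The sham change of 2.84 (SD 6.3) in the Background predicts the size of the problem.* It comes from week 12 of a 20-session trial in treatment-resistant patients and does not transfer to hours or days after four stimulations. The shared changes used above are therefore assumptions.
- *Day 28 was simply forgotten.* After the first two courses that visit is day 1 of the next course, so its absence from the duration list has a plausible reason.

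**Conclusion.** The point holds as a fault in the stated contrast and in the reading of the result, not in the arithmetic. Followed as written, the duration analysis credits placebo and time change to tDCS. If loss of significance is read as return, it also misses a persisting effect at n = 20 in about 75% (0.3) or 44% (0.5) of tests at each time point. The 59% to 75% figure for days 1 to 14 depends further on a constant change of 0.5 and correlations of 0.8 down to 0.3, neither of which is in the article. The two errors oppose each other, so the net direction of bias is unknown. The plan should be changed because the result is meant to set treatment spacing in the next trial and the sham data needed are already collected.

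**What to change.** **Duration.** Make the mixed model the stated analysis in place of the separate paired tests. Include condition (sham, OFC, SMA) by time, period, that course's own baseline and a random patient effect. Report the active-minus-sham difference with its 95% interval at each time point. Describe duration from those estimates and intervals, not from loss of significance and not from a 0.1 cut-off on the point estimate.

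**Day 28.** Report it as a supplementary time point, and note that after courses 1 and 2 the same score is the next course's baseline.

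**Neurocognitive tests.** Add the same sham-referenced, period-adjusted contrast of baseline-to-3 h change, and keep the planned comparison between targets.

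**Cost.** Wording and analysis only; no new visits or measurements. Intervals will be somewhat wider than for a within-arm change, and power stays low, so the duration result should be presented as an estimate with its uncertainty.

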A recent double-blind, randomised, and sham-controlled study investigated the efficacy of tDCS as add-on treatment for treatment-resistant OCD (*n* = 43) [38]. Over 20 consecutive weekdays of active or sham tDCS sessions (30 min, cathode was positioned over the SMA and the anode over the left deltoid) were administered, followed by an 8-week follow-up. Patients that received active tDCS achieved a significant reduction of OCD symptoms than those that received sham at week 12, with mean (*SD*) Yale-Brown Obsessive–Compulsive Scale (Y-BOCS) score changes of 6.68 (5.83) and 2.84 (6.3) points, respectively (Cohen’s *d*: 0.62 (0.06–1.18), *p* = 0.03), with no between-group differences in responders (four patients in the active tDCS and one in the sham group) [38]. There were no significant effects in reducing symptoms of depression or anxiety, and patients in both groups reported mild adverse events [38]. Also based on theoretical and computational models, authors suggest that overall cathodal tDCS may be better than anodal in treating OCD patients with an extracephalic montage [23, 33].

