### Participants

**Table Taba:** 

Inclusion criteria	Exclusion criteria
• Community-based service users, aged 18 years or older. If the clinician has any concerns about the participant’s cognitive competence for the completion of the CANTAB assessment, a MoCA (Montreal Cognitive Assessment) will be conducted. Only those with no indication of cognitive impairment will be eligible. • DSM-5 defined obsessive–compulsive disorder determined by a research psychiatrist using the structured interview for DSM-5 • Duration of symptoms >1 year (from medical history) • Baseline score ≥ 20 on the Yale-Brown Obsessive–Compulsive Scale (Y-BOCS) • Ongoing medication (SSRI, tricyclic antidepressant, antipsychotic, benzodiazepine) is allowed as long as the dose is kept stable for a sustained period before (≥ 6 weeks) randomisation and remains so throughout the study. • CBT is not allowed during or within 6 weeks of the start of the intervention. • If patients have changed medication in the last 6 weeks or are receiving treatment already with CBT, they will need to return to the clinic after 6 weeks and then be randomised.	• History of psychotic disorder (schizophrenia, psychotic symptoms, bipolar disorder), Tourette syndrome (tic disorders not amounting to Tourette syndrome will not be exclusionary), organic mental disorder, psychosurgery, personality disorder of borderline or histrionic type • Alcohol/substance-abuse disorders within the past 12 months • Any other DSM-5 disorder that is considered the primary focus of treatment • Severe depression, defined by a Montgomery-Åsberg Depression Rating Scale (MÅDRS) score > 30 at baseline • Actively planning suicide (scoring > 4 on item 10 of MÅDRS) or judged by the clinician to be at significant risk of self-harm • Received CBT involving exposure response prevention (ERP) from an accredited (British Association of Behavioural and Cognitive Psychotherapies (BABCP) approved or equivalent) therapist (e.g. IAPTs stage 2) in the last 6 weeks • Highly CBT resistant (inadequate clinical response, equivalent to < 25% improvement); ≥ 3 previous adequate (> 12 weeks) trials of CBT involving ERP from an accredited (BABCP-approved or equivalent) therapist • Highly medication resistant (inadequate clinical response, equivalent to < 25% improvement); ≥ 3 previous adequate (> 12 weeks) trials of any SSRI or clomipramine taken at optimal doses with adequate adherence • Needing regular psychotropic drugs other than permitted medication. • Currently involved in a treatment research study • Acute or unstable physical illness • Skull defects, or skin lesions on scalp (cuts, abrasions, rash) at proposed electrode sites • History of surgical procedure with implanted body materials or devices (e.g. metal, pacemakers) • Epilepsy or other clinically defined neurological disorder or insult • Inadequate understanding of English to give informed consent or such that the outcome measurement is impossible • Women of child-bearing age not using reliable contraception (e.g. oral contraception pill, intrauterine contraceptive device or condom). • Pregnant or breast-feeding women

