#### Analysis of secondary outcome

##### Effect of tDCS

To evaluate the effect of tDCS on OCD symptoms, Y-BOCS scores at all time points in the 3 treatment conditions (Sham, OFC, SMA) will be estimated. Comparison of the OFC and SMA targets will be considered using paired tests to determine if one target is superior to the other. As the sample size is small, it is not expected that this study will have the power to evaluate with certainty the superiority of either target, but may provide an indication for one stimulation target over the other.

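### Duration of the tDCS effect is read from each active target's own change from pre-stimulation, without the sham course, so any change shared with sham counts as duration

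*Protocol article*

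**What the plan says.** The duration analysis is set out in the protocol article under *Duration of effect*. The comparison is within each active target: "Change over time will be evaluated separately for the OFC and SMA targets using paired tests". The times considered are given as "identifying the time point (1, 2 and 4 h or 1, 7 and 14 days", and duration is the time point "at which the Y-BOCS returns to pre-stimulation levels". A model is optional: "A mixed model may be evaluated where this may provide additional useful information about the trajectory of the Y-BOCS score over time (growth models". No sham contrast is attached to it.

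The *Sample size calculation* section confirms that time-dependent Y-BOCS changes are to be examined with paired t tests, and gives their power for N = 20.

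Sham appears in two neighbouring sections. Under *Effect of tDCS*, "Y-BOCS scores at all time points in the 3 treatment conditions (Sham, OFC, SMA) will be estimated", but the only test named there is OFC against SMA. Under *Likely effect size*, "The observed and the lower limit for the effect size for the OFC and SMA targets will be evaluated with respect to the Sham condition", with the main focus at 24 h after the last stimulation.

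Table 1 has one assessment schedule for all three courses, sham included. *Secondary objectives* says that the duration result is meant to guide how treatments are spaced.

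**The concern.** A change from pre-stimulation within one course is the sum of the stimulation effect and everything else that moves the score in that course: expectation, attention, repeated rating and background change. The sham course is there to measure the second part. Under the stated method it is not used for the one analysis that dates the effect.

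The error can run either way. If patients improve for reasons shared with sham and stay improved, an inert target appears to have a lasting effect. If symptoms worsen in the background, a real effect appears to end too soon. Randomised order balances period trends across the three conditions, but only a contrast between conditions uses that balance. Because this is bias and not imprecision, more patients would only make a non-specific change more reliably significant. At stake is the spacing of treatments in the definitive trial.

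**Working it through.** **Inputs.** N = 20 and paired t tests (*Sample size calculation*). Alpha 0.05 is stated in that section for the main calculation. Sidedness is not stated; two-sided is assumed and checked in step 1.

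**Formula.** For a standardised within-patient change d, the paired t statistic is noncentral t with 19 degrees of freedom and noncentrality d × √20. Power is the probability that its absolute value exceeds 2.093, the 97.5th percentile of t on 19 degrees of freedom.

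**Step 1: reproduce the protocol's figures.**
- d = .65: noncentrality 0.65 × 4.472 = 2.907, power 0.787 (protocol .78).
- d = .77: noncentrality 0.77 × 4.472 = 3.444, power 0.904 (protocol .90).

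Both agree. A one-sided test would give 0.876 and 0.953, which do not fit. The two-sided paired t test is therefore the test the authors had in mind.

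**Step 2: apply it to a target that does no more than sham.** Suppose an active target and sham share the same change d from pre-stimulation. The within-target test cannot tell this from a stimulation effect, so its power at d is the chance of wrongly declaring an effect still present at that time point. The paired test of target change minus sham change has a true mean of zero, so it rejects at its nominal 5% whatever d is.

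| Shared change d | Noncentrality | Within-target test significant | Target-minus-sham test significant |
|---|---|---|---|
| 0.2 | 0.894 | 0.14 | 0.05 |
| 0.3 | 1.342 | 0.25 | 0.05 |
| 0.5 | 2.236 | 0.56 | 0.05 |
| 0.6 | 2.683 | 0.72 | 0.05 |

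The d values are assumptions shown as a range; the documents give no sham change for this schedule.

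**Step 3: the end of the effect.** The section does not say how a return to the pre-stimulation level is to be recognised. If the first non-significant test is used, a true change of d = 0.3 is missed with probability 1 − 0.247 = 0.753 at N = 20. Re-referencing to sham does not cure this by itself: a true target-minus-sham difference of the same standardised size would be missed equally often. The end of the effect has to be read from an estimate and its interval.

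**Step 4: cost in precision.** With equal SDs s of change in the two courses and correlation r between them, the SD of the difference is s × √(2(1 − r)). Relative to a single-course change this is 1.41 at r = 0, 1.18 at r = 0.3 and 1.00 at r = 0.5. The penalty is at most about 1.4 unless the course changes are negatively correlated.

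**The case against.** The strongest reply is that the consequence is limited. Duration is a secondary objective of a feasibility study, and *Progression to a full trial* does not list it among the principal data for the decision. Sham is also not lost from the evaluation: its scores are estimated at all time points, and both targets are compared with it mainly at 24 h. A reader would see the sham trajectory beside the active ones. This stands, and it lowers the severity. It does not remove the point, because no section makes sham the reference for duration. The optional growth model could include a sham contrast, but the protocol commits to neither the model nor the contrast.

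A reader might go further in two ways that the documents do not support.

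- **A rate of about one half.** The *Background* cites a sham-controlled trial with "score changes of 6.68 (5.83) and 2.84 (6.3) points, respectively" for active and sham. The sham figures give d = 2.84 / 6.3 = 0.45, and a within-target test would be significant with probability 0.48. But that change was measured at week 12, after 20 weekday sessions, in treatment-resistant patients. Here the readings run from 1 h to 14 days around four stimulations over two days, in patients described as not treatment-resistant. The post-stimulation hourly readings in Table 1 are on the Y-BOCS Challenge, not the Y-BOCS. The figure does not transfer. The 48% would in any case be the rate for one test alone, not the chance that the trial reports a lasting effect for an inert target.
- **Drift and regression to the mean as established.** Medication is allowed "as long as the dose is kept stable for a sustained period before" randomisation, with 6 weeks as the minimum, while the resistance exclusion counts a drug trial as adequate only beyond 12 weeks. One might infer that symptoms are still moving. The 12-week figure defines an adequate past trial; it does not say that scores change after week 6. The reference is also reset at each course, so only movement within about two weeks matters. Regression from the entry threshold of 20 would fall mainly on the first course, and less still if the threshold is applied at screening, since the Y-BOCS is repeated on Day 1. Both are possible; neither is shown to be likely.

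**Conclusion.** The point holds and should be fixed. Followed as written, the duration analysis attributes to tDCS any change that the active and sham courses share, although the plan collects the sham data needed to separate the two. The direction of the bias depends on whether the shared change is improvement or worsening.

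Its size cannot be fixed from the documents. The range of 14% to 72% against 5% applies to a single target at a single time point and assumes N = 20, a two-sided 5% test, an active target identical to sham, and a shared standardised change of 0.2 to 0.6. The argument about bias does not depend on any one of these values. The issue concerns how later treatments are spaced; it does not bear on the comparison with sham at 24 h or on the progression decision.

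**What to change.** Reword *Duration of effect*:

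1. At each time point, estimate the within-patient difference, target minus sham, in change from that course's own Day 1 pre-stimulation score.
2. Obtain it from a mixed model with condition, time, condition-by-time and period.
3. Analyse the hourly Y-BOCS Challenge readings separately from the Y-BOCS.
4. Read duration from this difference and its confidence interval over time, not from the first non-significant test.
5. Show within-target change from pre-stimulation as description only.

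This changes analysis wording only; it needs no new visits or data. The price is a larger standard error, up to about 1.4 times that of a one-course change if changes in the two courses are not negatively correlated, so duration will be dated less sharply.
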